#### Exploratory outcome measure

The exploratory outcomes are to evaluate the effects of HJD Formula Granules and HJD Elixation on oral and intestinal microflora, blood lipid, liver function, and urine function, specifically including:Detection of Salivary and intestinal microbiota and metabolite group.Blood lipid: TG, TC, LDL-c, HDL-c, Apo-A and Apo-B.Liver function: ALT, AST, GGT, albumin and bilirubin.Urine function: BUN, serum creatinine, eGFR, Uric Acid.

#### Safety capability evaluation

Safety capability evaluation refers to evaluating the tolerability and safety of HJD Formula Granules and HJD Elixation, specifically including:AEs/SAEs.Vital signs.Laboratory inspection.ECG.

### Data management

In order to facilitate the subjects to complete the whole study, they will be reminded at each visit point by phone or text message to come to the hospital for relevant examination. All data generated by subjects during the study shall be recorded in the CRFs in detail and truthfully.

With informed consent, uniformly trained investigators will gather data in compliance with the researchers’ manual and Standard Operating Procedure (SOP) formulated in advance. During this period, independent monitors review the data in real time to ensure the accuracy and completeness. In order to facilitate the later data check, all data modification should leave traces. In the case of paper CRFs, the original data should not be changed when the record is corrected or the errors are filled in. Instead, additional statements should be used. A line should be drawn on the original error and the correct data should be written next to it. If inputting the date on the electronic database, the database system should have the function of leaving traces to record the data before modification, modification reason, modification personnel and date as well as other information.

After the completion of data entry, data verification and cleaning are required. For the data with missing information, logical contradiction, error or uncertainty, the supervisor will deliver it to the researcher in the form of question list, and the researcher should answer the question. After verification, the database data will be revised. Any problems found during data verification and cleaning should be notified to the supervisor in time and the researchers are required to answer them. All kinds of questions and answers should use the question sheet, including the request for data supplement and review, etc. All query tables, and error data contents and modification results shall be recorded in detail and properly preserved.

The data of this research may be published in medical publications, but we will keep the subjects’ information secret as needed by law, and personal information about the subjects will not be revealed unless required by relevant laws.

### Statistical analysis

Primary, secondary, exploratory end points and safety assessments will be analyzed when the last patient completes the follow-up or drops out of the study. Analyses of clinical data will be performed by the principal investigator including subjects’ demographic, clinical, and laboratory data.

Continuous variables are used to evaluate the number of cases, mean, standard deviation, median, minimum, and maximum for demographic data and other baseline eigenvalues. Frequency and composition ratio are calculated using count and grade data. Descriptive results invole inferential statistical results (*p*-values).

For the analyses of laboratory data and clinical efficacy of drugs, chi-square test or Fisher’s exact test are used for counting data, while ANOVA and T test are used for measurement data. The grade data is analyzed by Ridit and CMH. The ratio or percentage of counting data is expressed, and the measurement data is expressed as mean ± standard deviation. All statistical tests are conducted by two-sided tests, with *P* < 0.05 indicating statistical significance. Multiple imputation will be used for missing data.

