### Participants

#### Sample size

Sample size is calculated by PASS 15.0 software, with the significance level of 0.05. A total of 189 cases (63 cases in each group) are required to detect inter-group differences in 2.6 mmol/L postprandial 2 h glucose, with a statistical power of 90%. The sample size calculation assumes a standard deviation of 2.0 mmol/L and a shedding rate of 20%.

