#### Inclusion criteria

Meet the diagnosis of “prediabetes”, namely, the criteria of “impaired fasting glucose” and “impaired glucose tolerance” in the classification of glucose metabolism state proposed by WHO in 1999 [28]. Which means that fasting glucose ≥6.1 mmol/L, < 7.0 mmol/L and/or OGTT 2-hour glucose ≥7.8 mmol/L, < 11.1 mmol/L.≥18 years old and < 70 years old.HBA1c ≤6.5%.Patients who have not participated in any interventional clinical study or clinical trial in the past 3 months.Patients who are able and willing to sign written informed consent and complete the study.

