
#### Primary outcomes

The primary outcome is to verify the clinical efficacy and possible mechanism of HJD in the treatment of prediabetes, and to prove the consistency of HJD Formula Granules with HJD Elixation.

It specifically includes the change value of HBA1c, FBG, 2hPG prior to and following treatment.

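### Glucose changes are to be compared by unadjusted ANOVA and t-test, which fixes the baseline slope at 1; baseline-adjusted ANCOVA would be as precise or more so and would remove the effect of chance imbalance

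*Protocol article*

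**What the plan says.** Under Primary outcomes, the endpoint is defined by change: "It specifically includes the change value of HBA1c, FBG, 2hPG prior to and following treatment". Under Statistical analysis, the method for continuous data is that "ANOVA and T test are used for measurement data". Neither ANCOVA nor any baseline covariate is mentioned anywhere in the article. The tests are two-sided at the 5% level.

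The Inclusion criteria admit patients on either glucose measure or both: "fasting glucose ≥6.1 mmol/L, < 7.0 mmol/L and/or OGTT 2-hour glucose" in the range 7.8 to below 11.1 mmol/L. The Randomization section gives 1:1:1 allocation with 63 per arm and names no stratification by baseline glucose.

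The Sample size section covers 2hPG only. The total of 189 is "required to detect inter-group differences in 2.6 mmol/L postprandial 2 h glucose, with a statistical power of 90" per cent, and "The sample size calculation assumes a standard deviation of 2.0 mmol/L and a shedding rate of 20" per cent. It does not say whether the SD of 2.0 refers to the change or to the follow-up value. No correlation between baseline and follow-up is given.

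**The concern.** Because entry is by fasting and/or 2-hour glucose, an arm can mix patients whose 2hPG is normal with patients close to 11.1 mmol/L, and the same holds for FBG. Those who start high have more room to fall and will tend to fall by regression to the mean alone. With 63 per arm and 20% loss, about 50 per arm are evaluable (63 × 0.8 = 50.4), so the arms can differ in baseline glucose by chance.

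A change score handles such a difference by subtracting it in full. If follow-up glucose tracks baseline less than one for one, that takes off too much: the arm that happens to start higher appears to improve more. ANCOVA estimates the slope from the data instead. It targets the same treatment difference and is normally more precise.

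The baseline values are already measured, so the precision costs nothing to recover. It matters most where the article gives no sample-size basis (FBG and HbA1c, both primary) and for the aim of showing that the two HJD forms are consistent, where the width of the interval determines what can be said.

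**Working it through.** **1. The plan's own sample size.** Inputs from the Sample size section: difference 2.6, SD 2.0, alpha 0.05 (two-sided, from Statistical analysis), power 90%, dropout 20%.

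n per arm = 2 × (1.960 + 1.282)² × 2.0² / 2.6² = 12.4, rounded up to 13. Dividing by 0.8 gives 17 randomised per arm, 51 in total. The stated 63 per arm (189) is not reproduced. It is reproduced with a difference of 1.3: 2 × (1.960 + 1.282)² × 2.0² / 1.3² = 49.7, so 50 evaluable and 63 randomised. It is equally reproduced with an SD of 4.0. That mismatch is a separate matter; it is noted here because it governs which power figures can be used.

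Power at the stated difference with 50 per arm and an unadjusted comparison: 2.6 / (2.0 × √(2/50)) = 6.5, and 6.5 − 1.96 = 4.54, which is a power above 99.99%. Adjustment cannot visibly improve on this.

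**2. Information lost by fixing the slope at 1.** Let r be the baseline-to-follow-up correlation and k the ratio of baseline SD to follow-up SD. In units of the follow-up variance:

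- change score: variance proportional to 1 + k² − 2rk
- ANCOVA: variance proportional to 1 − r²
- share lost by the change score: (k − r)² / (1 + k² − 2rk)

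With equal SDs (k = 1) the loss reduces to (1 − r)/2. Neither r nor k is in the document; both are assumed below.

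| r | k = 1 | k = 0.75 | k = 0.5 |
|---|---|---|---|
| 0.3 | 35% | 18% | 4% |
| 0.5 | 25% | 8% | 0% |
| 0.7 | 15% | 0.5% | 7% |

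Worked example, r = 0.3 and k = 0.75: 0.45² / (1 + 0.5625 − 0.45) = 0.2025 / 1.1125 = 18%. Simulation with 50 per arm and 20,000 runs at k = 1 gave 34%, 25% and 14%, slightly below the formula because the slope has to be estimated.

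**3. Effect of chance imbalance.** The true slope is r/k. Per 1 mmol/L of baseline difference between arms, the change-score estimate moves by r/k − 1.

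- k = 1: −0.70, −0.50 and −0.30 at r = 0.3, 0.5 and 0.7. Simulation gave −0.70, −0.50 and −0.30; under ANCOVA the movement was about 0.
- k = 0.75: −0.60, −0.33 and −0.07.

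The negative sign is over-correction. If r exceeds k (for example r = 0.7, k = 0.5, slope 1.4), the slope is above 1 and the change score under-corrects instead.

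**4. Interval width for a pairwise comparison such as Granules versus Elixation.** Assume that 2.0 is the SD of the 2hPG change and that 50 per arm are evaluable. The unadjusted 95% half-width is 1.984 × 2.0 × √(2/50) = 0.79 mmol/L. Multiplying by √(1 − loss):

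- k = 1: 0.64, 0.69 and 0.73 mmol/L at r = 0.3, 0.5 and 0.7
- k = 0.75: 0.72, 0.76 and 0.79 mmol/L

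**The case against.** The strongest reply is that nothing here is invalid. Under randomisation a t-test on change has the right type I error, and ANCOVA is an efficiency choice. The statistical section is one general sentence in a condensed article, and model covariates are often left to the analysis plan. The first part stands, and it limits the weight of the point. The second stands only in part: the article does not stay silent but names a method for this type of endpoint, and that method is unadjusted.

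Several stronger readings are tempting and are not supported:

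- A reader might infer that the plan ignores baseline or leaves imbalance uncorrected. It does not: a change score subtracts baseline. The fault is the fixed slope, which over-corrects when the true slope is below 1. Uncorrected would describe a comparison of raw follow-up values, which is not planned.
- A reader might take a loss of 15-35% as a property of this trial. It needs equal SDs as well as r of 0.3 to 0.7. Eligibility caps baseline glucose (2hPG below 11.1 or FBG below 7.0 mmol/L) but not follow-up, so the baseline SD may well be the smaller, and the loss can then be close to zero.
- A reader might claim a power gain from 90% to 94-98%. That uses a 1.3 mmol/L difference, which is worked back from the sample size and is not stated in the protocol. It also strains against eligibility. With equal SDs and a change SD of 2.0, the baseline SD would be 2.0/√(2(1 − r)) = 1.69, 2.00 or 2.58 mmol/L, whereas a uniform spread over 7.8 to 11.1 has an SD of only 0.95. Allowing for fasting-only entrants with an assumed spread from 4 to 11.1 gives 2.05.

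It is also fair to say that the article sets no margin or confidence interval for Granules versus Elixation. The narrower interval is therefore a benefit to a comparison whose decision rule is not stated, not the repair of a stated rule.

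**Conclusion.** The point holds as one of efficiency and conditional bias. The article pairs change-score primary outcomes with unadjusted tests although baseline glucose is available. The information lost relative to ANCOVA is roughly 0-35%: 35% to 15% for r of 0.3 to 0.7 with equal SDs, and 18% to about 0% with a baseline SD of 0.75 of the follow-up SD. Both r and the SD ratio are assumptions. The loss formula is never negative and is zero only if the true slope equals 1, so apart from one degree of freedom ANCOVA is never the less precise choice.

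The documents do not support saying that the planned tests are invalid or that 2hPG is underpowered because of them; at the stated 2.6 mmol/L its power is above 99.99% either way. The practical benefit is tighter estimates for FBG and HbA1c and for Granules versus Elixation, and estimates that do not move with chance baseline differences. This is a change that should be made, not one on which the trial's validity depends.

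**What to change.** Replace the general sentence, for the glucose outcomes, with a pre-specified ANCOVA: the day-84 value (or the change) on treatment arm, with that outcome's own baseline value as covariate. With baseline in the model, both versions give the same treatment difference, so change can still be reported. Apply the model to HbA1c, FBG and 2hPG and to the other continuous change outcomes (weight, BMI, C-peptide, cytokines). Report adjusted differences with 95% CIs for each HJD arm versus placebo and for Granules versus Elixation. Fix this before unblinding, so that adjustment cannot be chosen after the results are seen.

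Cost: one line of analysis text and one degree of freedom per model; no new data and no change to visits or sample size.

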### Adverse events

Although no serious adverse events have been reported with this formulation in previous studies, subjects may have vomiting, diarrhea and other adverse reactions because of individual difference.

Specifically, adverse reactions include clinical symptoms (such as nausea, fatigue, dizziness, abdominal pain, and itching), signs (such as jaundice, rash, and fever), diseases and abnormal laboratory tests, etc. Adverse events are classified as “mild”, “moderate”, or “severe” based on severity. All adverse reactions and their incidence, duration, severity and treatment measures, ending, and the relationship between drug and its dosage will be detailed and fully documented in the CRFs. When a patient experiences an adverse event and does not show significant remission after treatment, the researcher will inform the chief investigator and the ethics committee. Then modification or termination will be conducted to ensure the safety and interests of the subject.

### Trial monitoring

The academic committee of Shenzhen TCM Hospital is responsible for reviewing the scientific nature and compliance of the protocol and making recommendations for the continuation or termination of the study. The ethics committee is responsible for reviewing the rationality of the protocol and safeguarding the rights and interests of the subjects. Both members are independent of the sponsors and researchers, and there is no conflict of interest.

## Discussion

The study’s goal is to investigate the effectiveness and difference of TCM decoction and granule in the management of prediabetes, to clarify whether HJD can adjust fat preferences, and oral and intestinal microbiota of prediabetic patients, and subsequently to slow or prevent the transition from prediabetes to diabetes.

Elixation and granule are the two main dosage forms of TCM treatment, which are widely used in clinic. However, there are few placebo-controlled studies on TCM decoction for prediabetes. After treating prediabetic rats with TCM granules, Wang and colleagues [34] found that TCM granules significantly improved body weight and glucolipid metabolism in rats, and increased insulin sensitivity to an effect similar to that of rosiglitazone. Wei [35] also confirmed in a multi-center trial that TCM granules could restore normal blood glucose in 41.8% of prediabetic patients (27.8% in the control group) after 12 months of intervention. However, the follow-up showed that the granules group had weak lasting effect, and there was no improvement in subjects’ HBA1c levels. Therefore, this study expands the function of TCM elixation in the management of prediabetes, and hopes to significantly improve the symptoms and indicators of prediabetes patients.

Eating habits are closely related to people’s life. People often crave fat because it provides more calories and pleasure [36]. However, high-fat diets also lead to weight gain and decreased sensitivity to fat, which further increases people’s intake of high-fat diets [37, 38]. Poor diet quality has been reported to significantly increase the risk of prediabetes (OR: 1.45, 95%CI: 1.29–1.63) [39], and also affect the changes of oral and intestinal flora [40, 41].

Human saliva contains abundant biological information, and the oral flora can reflect various physiological and pathological changes of the human body. Amr and Kornwipa [42, 43] found that the number of species in oral saliva decreased with the progression of diabetes, and that diabetics exhibited the largest pathogenic microbiome. However, the sample size of their researches was small, the changes of oral microflora in prediabetic patients need to be further explored in a larger sample.

In addition, hyperglycemia will lead to abnormal intestinal flora, further destroy the intestinal barrier, and cause damage to glucose metabolism and immune homeostasis. The study confirmed that after 12 weeks of supervised training, prediabetic patients experienced significant changes in their gut microbiota, as well as remarkable improvements in insulin sensitivity and other metabolic characteristics. After excluding the interference of body weight and visceral fat, correlation analysis confirmed a significant association between the two [44]. What’s more, prediabetes patients had increased multiple butyrate-producing bacteria after inserting the gut microbiota of a healthy person, which could convert fiber into short-chain fatty acids, and then released GlP-1 to suppress appetite and promote weight loss through gut–brain neural circuit [45].

In previous studies, we found that HJD has a good therapeutic effect on metabolic diseases [25–27, 29, 30], and have improved the preparation process of TCM placebo which had been applied for a patent [46], providing a corresponding clinical basis for this study. Therefore, we designed this study to further evaluate the effect of HJD Elixation and Formula Granules in treating prediabetes, the results may also discover the effect of HJD in oral LA threshold, dietary preference, saliva and intestinal microbiota of prediabetes patients, thus to further explain its potential therapy mechanism.

## Data Availability

Following the completion of the present research, the datasets used and/or analyzed will be made accessible to the corresponding author upon reasonable request.

## Abbreviations

TCM: Traditional Chinese medicine
HJD: Huoxue-Jangtang Decoction
ADA: American Diabetes Association
CRF: Case Report Forms
3-AFC: 3-alternative forced-choice procedure
LA: Linoleic acid
FBG: Fasting blood glucose
2hPG: 2-hour postprandial blood glucose
HbA1c: hemoglobin A1c
FID: Free induction decay
PCA: Principal component analysis
ECG: Electrocardiogram
SOP: Standard operating procedure
